### Objectives and hypotheses

The primary objective of this study is to assess whether the ENGAGE-MUSIC/SPANISH program leads to cognitive gains in episodic memory at the immediate follow-up assessment in older adults with a subjective memory complaint when compared with an active control condition. The secondary objectives of this study are: to assess whether these cognitive gains are maintained at the 24-month follow-up; to determine the effect of the program on attentional control, psychological health, activities of daily living, and brain structure and function as measured by magnetic resonance imaging (MRI); and to identify if the characteristics of participants modulate outcomes. Finally, the study will examine whether music and Spanish lessons produce different effects on the primary and secondary outcome measures.

It is expected that the ENGAGE-MUSIC/SPANISH training will show evidence of efficacy: persons enrolled in the ENGAGE-MUSIC/SPANISH training program will have larger gains in the memory composite measure following training than participants enrolled in the active control condition. Secondary hypotheses involve maintenance of training gains, and effects of training on attentional control, daily functioning, well-being, and brain structure and function. It is hypothesized that training effects on the memory composite will be maintained at the 24-month follow-up assessment. As the ENGAGE-MUSIC/SPANISH program includes a component of attention training, it is expected that measures of attentional control will improve. It is also expected that cognitive improvement will transfer to measures of activities of daily living (e.g., managing finances, medication, grocery shopping) and that it will increase indicators of psychological health. Also, the ENGAGE-MUSIC/SPANISH training will result in measurable effects on the brain as assessed by both structural (cortical thickness and regional grey matter volume) and task-related MRI activation, and that these changes will be correlated with improved cognition. Finally, we hypothesize that participant characteristics (sex, age, education) will modulate efficacy and transfer.

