### Adherence to treatment and retention

A number of strategies will be used to reduce attrition and promote retention over the 24-month follow-up. The coordinator of the study will be available by phone to discuss potential problems. In case of reduced adherence, we will contact the participant or his/her informant to identify the reasons and/or barriers that reduce their attendance and help identify solutions. The choice of a preference trial where participants are given the possibility to exclude an activity they dislike was also made to increase adherence to treatment. The team will remain in contact with the participants during the long-term follow-up through yearly telephone calls and greeting cards for the festive season. The attrition rate is expected to be approximately 18% based on our most recent study which used a similar program [10]. The characteristics of those who withdraw will be analyzed and intent-to-treat analyses will be used. Participants who withdraw from the program will be invited to come for follow-up assessments.

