### Outcome variables

Evaluations will be conducted at the Centre for Memory and Aging, Baycrest Health Sciences, and Sunnybrook Hospital for Toronto participants. In Montreal, they will be conducted at the IUGM. Outcome measures will be tested at three time points: before the intervention (PRE; time frame within 12 weeks before intervention starts), just after the intervention at the 4-month follow-up (F4; time frame within 8 weeks after the end of the intervention), and at the 24 follow-up (F24; time frame 2 years after PRE ± 3 months). Participants are not allowed to participate in other research programs or lifestyle interventions between baseline and the first follow-up (F4), but they can get involved in any activities between F4 and F24.

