#### Analysis of efficacy and maintenance on primary and secondary outcomes

Descriptive statistics will be used for demographics and baseline characteristics, with means and standard deviations given. We will compare the intervention groups on these variables using one-way analysis of variance (ANOVA) for continuous variables and Chi-square analyses for discrete variables. The primary efficacy analysis will be done with a modified intention-to-treat approach retaining all participants and identifying the characteristics of participants withdrawing from follow-up as well as the causes for withdrawal. As proposed for preference trials, a first set of analyses will only use fully randomized participants. This will be followed by analyses of the comprehensive cohort which will include those in the preference arms.

The linear mixed model will be used to assess the efficacy of the intervention. The mixed linear model has many advantages over typical ANOVA; it handles correlated data and is robust to unbalanced design, hence allowing for the inclusion of all participants, including those missing at follow-up. Missing data will not be imputed as mixed models use all available data, including those from participants having incomplete follow-up. The fixed effects will be intervention (ENGAGE SPANISH/MUSIC versus ENGAGE DISCOVERY), time (PRE versus F4), and their interaction. A significant interaction is expected if the intervention is more beneficial than the control condition. When an interaction is found, we will look at whether there is a significant difference between PRE and F4 in each group and assess group differences on change scores at post-training ([PRE – F4]/|PRE|). Efficacy is supported if the F4 change score is larger in the intervention group than in the control group. All analyses will be adjusted for site and baseline performance.

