A similar approach will be taken for most of our secondary objectives. A set of secondary objectives of the study is to assess the long-term maintenance of the effect of the training. This will use a mixed linear model to test long-term maintenance of intervention effects (PRE versus F24) on primary outcome, as well as separate models (with three levels of time: PRE, F4, and F24) on measures of attentional control, psychological health variables (anxiety/depression, apathy, quality of life, help seeking), everyday functioning measures (MMQ, AMQ, ADCS-ADL-PI, the Cognitive Activities Questionnaire, Memory Toolbox, and DAFS-R), and on the structural brain measures (hippocampal volume and cortical thickness). Because the Jessen questions about subjective complaint are dichotomous, Chi-square analyses will be used to compare the number of participants who have a memory complaint before and after the intervention as a function of condition. For exploratory purposes and to inform future interventions, the above analyses will be repeated comparing the music and Spanish arms. The *p* values will be presented before and after adjustment for multiple comparisons based on the Hochberg procedure. All statistical tests will be two-tailed and a *p* value of less than 0.05 will indicate statistical significance. All computations will be made with SPSS version 23.0 (SPSS Inc., Chicago, IL, USA).

Functional MRI data will be subjected to standard pre-processing steps using SPM8 (i.e., motion correction, slice timing correction, co-registration with anatomical T1 image, spatial normalization). First level (individual) analyses will involve general linear models with box-car responses, convolving the time course of the event-related response per condition with the canonical hemodynamic response function. Second level (group) analyses will treat participants as a random variable, with each contrast tested at *p* < 0.05 after whole-brain, family-wise error correction. A cluster threshold of 50 or more contiguous voxels will be applied.

Preliminary analyses of the descriptive characteristics and baseline performance will be done after full recruitment is completed. Analysis of efficacy will be done at the end of the 4-month follow-up and long-term analyses will be done at the end of the 24-month follow-up.

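### The 24-month model for the memory composite leaves out F4, so it gives no formal estimate of how much of the gain is kept and sets aside data on people who drop out after F4

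*Protocol article*

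**What the plan says.** All places are in the protocol article.

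- **Objectives and hypotheses.** The first secondary objective is "to assess whether these cognitive gains are maintained at the 24-month follow-up". The gains meant are those of the primary objective, at the immediate follow-up. The matching hypothesis speaks of training effects on the composite lasting to 24 months.
- **Outcome variables.** "Outcome measures will be tested at three time points": PRE, F4 and F24.
- **Analysis of efficacy and maintenance on primary and secondary outcomes.** The primary model has, besides intervention, "time (PRE versus F4), and their interaction". For long-term maintenance the plan is a "mixed linear model to test long-term maintenance of intervention effects (PRE versus F24) on primary outcome". The same sentence goes on: "as well as separate models (with three levels of time: PRE, F4, and F24) on measures of attentional control", followed by psychological health, everyday functioning and structural brain measures.
- **Missing data, same section.** "Missing data will not be imputed as mixed models use all available data, including those from participants having incomplete follow-up".
- **Adherence to treatment and retention.** "The attrition rate is expected to be approximately 18% based on our most recent study which used a similar program". The figure is not split by visit.

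**The concern.** The outcome that matters most gets a leaner long-term model than the secondary measures, and no reason is given. Two things follow.

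First, without F4 in the model there is no F4-to-F24 contrast. That contrast says how much of the early gain survives, and the objective is worded around keeping that gain.

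Second, a participant who completes F4 and then leaves contributes only PRE. The likelihood then recovers the missing F24 score from PRE and arm alone. Drop-out must be unrelated to F4 once PRE and arm are known, a stronger requirement than in a model that contains F4. The plan's case for not imputing is that all available data are used, and here they are not. At stake are the size of the 24-month effect on the main outcome and what may be said about its durability.

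**Working it through.** **1. Inputs.** From the protocol article: 144 participants and 2:1 allocation (144 × 2/3 = 96 and 144 × 1/3 = 48); attrition about 18% (144 × 0.18 ≈ 26 people); F24 set at 24 months after baseline, so about 20 months after F4. The article gives no numeric effect size, visit correlation or power for the 24-month analysis, so there is no planned figure to reproduce. Effects, correlations and drop-out mechanisms below are assumptions.

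**2. Reading of the text.** The primary model writes its two time levels as PRE versus F4. The maintenance model for the composite uses the same notation with F24, and the sentence then sets it apart from models with three levels. The plain reading is a two-level factor without F4.

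**3. What the two-level model can show.** Let δ4 and δ24 be the arm differences in change from PRE to F4 and from PRE to F24. Retention is δ24 − δ4. With δ24 = 0.3 SD:

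| δ4 | PRE/F24 interaction | δ24 − δ4 | Share kept |
|---|---|---|---|
| 0.3 | 0.3 | 0.0 | 0.3/0.3 = all |
| 0.6 | 0.3 | −0.3 | 0.3/0.6 = half |
| 0.9 | 0.3 | −0.6 | 0.3/0.9 = one third |

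The PRE/F24 model returns the same answer in all three rows. The primary model estimates δ4 separately, so a point estimate is available by subtraction. Its variance is Var(δ4) + Var(δ24) − 2 Cov(δ4, δ24), and two separate models do not supply the covariance.

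**4. Effect of losing F4 under drop-out.** With everyone seen at F4 and a common unstructured covariance, maximum likelihood amounts to this: regress F24 on arm and PRE (two-level), or on arm, PRE and F4 (three-level), among those seen at F24; predict F24 for everyone; take the arm difference in mean predicted F24 minus PRE. Simulated trials of 96:48, at least 4,000 per scenario in rows 1 to 4, true F24 effect 0.40 SD, gave these mean two-level estimates (correlations in the order PRE–F4, PRE–F24, F4–F24):

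| Assumed setting | Loss | F4-dependent, both arms | Control arm only | Intervention arm only |
|---|---|---|---|---|
| 1. Correlations 0.5–0.75 | 15–30% | 0.388, 0.384, 0.380 | 0.348, 0.320, 0.290 | not run |
| 2. 0.65/0.55/0.70, dependence on F4 residual | 18%; 30% | about 0.40 | 0.344; 0.311 | 0.457; 0.491 |
| 3. 0.7/0.6/0.7, logistic slope 1 | 18%, all after F4 | 0.388 | 0.346 | 0.441 |
| 4. As 3 | 9% before F4, 10% after | 0.390 | 0.364 | 0.425 |
| 5. Further check | 17–20% after F4 | 0.383 | 0.342 | 0.445 |

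The three-level estimates in settings 1, 2 and 5 were 0.397 to 0.404. Under random loss the two-level estimates were about 0.40 (setting 2) and 0.405 (setting 5).

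Relative bias at about 18% loss (settings 2, 3 and 5):
- both arms: from 0 to (0.400 − 0.383)/0.40 = 4%;
- control arm only: (0.400 − 0.346)/0.40 = 13.5% to (0.400 − 0.342)/0.40 = 14.5%, downward;
- intervention arm only: (0.441 − 0.400)/0.40 = 10% to (0.457 − 0.400)/0.40 = 14%, upward.

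If about half the loss comes before F4 (setting 4), one-arm bias falls to 9% downward and 6% upward. At 30% (setting 2) it rises to 22% and 23%. Setting 1 gives 3–5% for both arms and 13–28% for control only over its range of loss.

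**5. Sensitivity.** With a true effect of 0.30 SD, 18% loss and a steeper slope (1.5) in the intervention arm only, the bias was +0.06 to +0.10 SD. With slope 1 in both arms it was −0.015 to −0.03 SD. The 10–15% is therefore not an upper bound.

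**6. Precision.** Under random loss of 18% the three-level variance was 0.976 or 0.914 of the two-level variance, depending on the correlations. The two-level standard error is thus 1/√0.976 = 1.012 to 1/√0.914 = 1.046 times as large. Setting 1 gave 1.013 to 1.048.

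**The case against.** **The two-level test is legitimate.** A training effect is a between-arm effect, and the PRE/F24 interaction tests whether it exists at 24 months. This stands. A reader might infer that the plan cannot test maintenance at all; the article does not support that, because persistence of an arm difference is one fair meaning of the word. What is missing is a formal estimate of retention.

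**The bias is hypothetical and small against the noise.** This largely stands. With a standard error of about 0.17 (setting 3), the both-arm bias is 0.012/0.17 = 0.07 standard errors and the one-arm bias is 0.041/0.17 = 0.24 to 0.054/0.17 = 0.32. Nothing in the article points to F4-dependent loss among controls alone: they are not told that theirs is the control condition, and people who withdraw are invited to follow-up. The Discussion's remark that cognitive training may be tedious and raise withdrawal would, if anything, concern the intervention arm. A reader might infer that the plan understates the 24-month effect, but the sign is unknown.

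**There is a rationale.** Efficacy is analysed after F4 and long-term effects after F24. A separate PRE/F24 model aims directly at 24 months, whereas an omnibus three-level interaction could be significant because of F4 alone. That argues for naming the contrast, not for leaving F4 out.

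**The bracket might denote a contrast within a three-visit model.** This is possible in a condensed article, but the wording elsewhere in the section makes it the weaker reading. If it was meant, the sentence still needs correcting.

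**Conclusion.** The point holds in a limited form and concerns a secondary objective. As written, the 24-month model for the composite answers whether an arm difference exists, but not, with a standard error, how much of the F4 gain is kept. That gap needs no missing-data assumption. The set-aside F4 scores also run against the plan's own argument for not imputing.

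The bias is conditional on drop-out that depends on F4 beyond PRE and arm: 0–5% of an assumed 0.4 SD effect if the dependence is alike in both arms, and roughly 10–15% at about 18% loss after F4 if it is in one arm only, in either direction. Random loss costs only precision.

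Two further inferences should be resisted. The three-level model is not unbiased in general: it was so here because loss was made to depend on observed scores, and it would not remove bias from unobserved decline in the 20 months after F4. Nor does every other repeated outcome get three levels: the dichotomous memory-concern questions get a chi-square analysis, and task fMRI is done only at PRE and F4.

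**What to change.** Fit one mixed model with PRE, F4 and F24 and an unstructured covariance to the memory composite, using the three time levels already planned for most other outcomes. Name two arm contrasts in advance: PRE to F24 as the persisting effect and F4 to F24 as retention. Base the conclusions on these contrasts and not on the omnibus interaction. Leave the primary PRE/F4 analysis unchanged.

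The cost is about one sentence in the analysis section. The F4 scores are collected anyway, so no visits or participants are added.

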### Randomization and blinding procedure

The opportunity to exclude either music or Spanish training will be offered to all participants prior to randomization. Randomization will be done individually (i.e., one participant at a time as they enter the study) with random lists of binary numbers. Lists will be generated using the Random.org online software. Randomization will be controlled by a person from the Montreal site who is independent of the study. A first randomization will allocate participants to the intervention or control condition by matching the sequential list of participant identification codes with the list of random condition allocation. This will be done with a 2 to 1 ratio between intervention and control conditions. A second randomization will be used to allocate participants in the intervention condition to either Spanish or music training, using a 1 to 1 ratio for participants who did not exclude either of these two activities. Participants randomized in the intervention condition who excluded music or Spanish training will be placed in their preferred activity. Recruiting staff will contact (via telephone) the trial allocation office in charge of randomization once a participant has consented to participate and will be given the allocation. The allocation and sequence of allocation will be concealed from evaluators.

Evaluators who will be assessing the participants will be blinded to the hypotheses and to the group assignment of participants. Participants will be asked not to mention their group assignment to evaluators. Any breach of this group assignment blinding by participants will be noted, but since evaluators will be blinded from the hypotheses this should have minimal effect on integrity. Activity leaders will not be blinded to the study hypotheses. Although participants will know that they are in the Spanish, music, or documentary discussion group, they will not be informed of the study hypotheses, i.e., participants assigned to ENGAGE-DISCOVERY will be unaware that it is an active control condition. To keep participants blinded from the hypotheses and reduce the likelihood that the expectations of participants bias the data [29], close attention will be paid to ensure that the content of the intervention and the wording of recruitment documents and consent forms do not convey the expectations that one condition is inferior in terms of its effect on the brain and cognition.

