### Statistical analyses

#### Sample size

The trial will recruit 144 participants. The sample size was estimated from a power analysis with G*power based on pilot findings collected with the MEMO program [10, 12], using word recall and face-name associations tasks. The MEMO program is included as part of the formal training in this intervention in addition to stimulating leisure activities and attentional training. Therefore, it is reasonable to expect that the effect should be at least as large as the one observed when using MEMO alone. The pilot data indicated a medium effect size for the group-by-time interaction when examining face-name association and a large effect size when examining word recall (see Additional file 2: Appendix 2). It shows that the sample size would be sufficient to detect an interaction given a similar effect size considering the same attrition rate that we obtained in this prior study (18%). Half of the sample will be recruited in Montreal and the other half will be recruited in Toronto.

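### For the secondary outcomes, the stated test of long-term maintenance does not isolate the 24-month visit, and the only written follow-up step concerns the 4-month visit

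*Protocol article*

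**What the plan says.** All of this is in the protocol article, Statistical analyses, under the heading on efficacy and maintenance.

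- **Objective.** "A set of secondary objectives of the study is to assess the long-term maintenance of the effect of the training".
- **Primary outcome.** Maintenance is tested in a mixed model with two time levels, PRE and F24.
- **Secondary outcomes.** The same sentence goes on "as well as separate models (with three levels of time: PRE, F4, and F24) on measures of attentional control", then lists psychological health, everyday functioning, and hippocampal volume and cortical thickness. The yes/no memory-complaint questions are handled separately by Chi-square and are not part of this point.
- **Test.** The secondary objectives are said to follow a similar approach to the primary efficacy analysis. There the fixed effects are intervention, time and their interaction, and the interaction is what is tested.
- **Follow-up step.** "When an interaction is found, we will look at whether there is a significant difference between PRE and F4 in each group", together with a group comparison of change scores at post-training. No corresponding step for F24 is written.
- **Error level.** "All statistical tests will be two-tailed", and a p "value of less than 0.05 will indicate statistical significance". Hochberg-adjusted p values are shown beside the unadjusted ones.

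**The concern.** With two time levels the intervention-by-time interaction is a single contrast, so a PRE-versus-F24 model answers whether the arms differ in change at 24 months. With three levels the interaction has 2 degrees of freedom. Its null is that the arms have the same change from PRE at F4 and also the same change from PRE at F24. It is false as soon as the arms differ at F4, even if they have fully converged by F24.

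One sentence therefore sets an F24-specific test for the primary outcome and a non-specific one for the listed secondary outcomes, under the same maintenance objective. The written follow-up step does not close the gap, because it looks at F4.

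Durability is one of the knowledge gaps that the Background says the trial is to fill. Under Outcome variables, participants may take up any activity between F4 and F24, so convergence of the arms by F24 is a realistic pattern.

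**Working it through.** The article gives no power figure, effect size or correlation for the secondary outcomes, so there is no stated figure to reproduce. The check asks how the 2-df interaction and the 1-df F24 contrast behave when an effect has faded and when it has been kept.

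**Inputs from the article**
- Sample size: "The trial will recruit 144 participants".
- Allocation: "This will be done with a 2 to 1 ratio between intervention and control conditions", so 96 and 48.
- Attrition: "The attrition rate is expected to be approximately 18% based on our most recent study which used a similar program". Then 144 × 0.82 = 118.08, split 2:1 as 78.7 and 39.4, taken as 79 and 39.
- Structural MRI: 54 participants, 27 per condition (Brain structure). Applying the same 18%, 27 × 0.82 = 22.1, taken as 22 per arm.
- Two-sided 0.05.

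**Assumptions**
- Outcome SD 1, and equal correlation ρ between any two visits, from 0.5 to 0.8.
- Arm effect at F4 of d = 0.5 SD (0.3 SD as a smaller case).
- Complete data on those retained, and no multiplicity adjustment.

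**Formulas**

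Let k = 1/n₁ + 1/n₂. The two arm differences in change, (F4 − PRE) and (F24 − PRE), each have variance 2(1−ρ)k and have covariance (1−ρ)k. For true effects (a, b) at F4 and F24, the noncentrality of the 2-df test is

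λ = 2(a² − ab + b²) / [3(1−ρ)k].

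- Faded, (a, b) = (d, 0): λ = 2d² / [3(1−ρ)k].
- Kept, (a, b) = (d, d): a² − ab + b² = d², so λ is the same.

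Under equal correlations the interaction thus has identical power for an effect that has vanished and one that is intact. Power comes from the noncentral F with 2 and n₁ + n₂ − 3 degrees of freedom. The F24 contrast has noncentrality b / √[2(1−ρ)k] on n₁ + n₂ − 2 degrees of freedom. When b = 0 it rejects at its nominal 5%.

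**Example.** For 79 and 39, k = 0.0383. With d = 0.5 and ρ = 0.5, λ = 0.5 / (3 × 0.5 × 0.0383) = 8.70, and power is 74%.

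**Results, 79 versus 39**

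| d at F4 | ρ | Interaction, faded | Interaction, kept | F24 contrast, faded | F24 contrast, kept |
|---|---|---|---|---|---|
| 0.5 | 0.5 | 74% | 74% | 5% | 72% |
| 0.5 | 0.6 | 84% | 84% | 5% | 81% |
| 0.5 | 0.7 | 93% | 93% | 5% | 90.5% |
| 0.5 | 0.8 | 99% | 99% | 5% | 98% |
| 0.3 | 0.5 | 33% | 33% | 5% | 33% |
| 0.3 | 0.8 | 70% | 70% | 5% | 67% |

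Simulation (20,000 trials per scenario, ρ 0.5 to 0.7) agrees. For d = 0.5 faded, the interaction rejects in 74%, 84% and 93% and the F24 contrast in 5.1% to 5.2%.

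**Results, structural MRI subgroup, 22 per arm, d = 0.5 faded.** Here k = 0.0909. The interaction rejects in 36% at ρ = 0.5, 56% at ρ = 0.7 and 75% at ρ = 0.8, against about 5% for the F24 contrast.

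**If an F24 comparison is added after the interaction.** Requiring both to be significant gives 5.0% to 5.1% for d = 0.5 faded over ρ 0.5 to 0.7.

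**The case against.** The strongest reply is that the article nowhere says a significant three-visit interaction will itself be declared maintenance. In the primary analysis the interaction only opens the way to follow-up comparisons, and the efficacy conclusion rests on a visit-specific change score. A similar approach would naturally mean the same step at the visit of interest. The F4 wording was written for a PRE-versus-F4 model, and copied literally it would not suit the primary outcome's PRE-versus-F24 model either. With an F24 step added, the error rate is about 5%. This stands. A reader might infer that 74% to 99% is the rate at which maintenance would be falsely claimed. The documents do not support that: it is the rate at which the stated test is significant when an F4 effect is real and has faded.

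A reader might also infer that the three-visit interaction would block detection of a real F4 effect on these outcomes. The article places the efficacy analysis at the end of the 4-month follow-up and the long-term analyses at the end of the 24-month follow-up. A test that needs F24 data cannot gate the earlier analysis, so that reading falls.

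It can further be said that the one explicit maintenance hypothesis under Objectives and hypotheses concerns the memory composite, that a three-visit model suits the general aim of describing effects on other outcomes, and that contrasts are commonly named in an analysis plan that is not shown. The first two are fair, but the analysis section itself places the three-visit models under the maintenance objective. On the third, the article is not simply silent. It fixes the model and the test, and treats the primary outcome differently in the same sentence.

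**Conclusion.** The point holds in a limited form. For attentional control, psychological health, everyday functioning and structural MRI, the test stated for long-term maintenance is not tied to F24, and the only written follow-up concerns F4. Under equal correlations between visits, that test is exactly as likely to be significant for a vanished effect as for an intact one: 74% to 99% for a 0.5 SD effect at F4 with 79 and 39 completers, and 36% to 75% in the MRI subgroup at 22 per arm. The F24-minus-PRE contrast rejects in about 5% when the effect has faded.

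The percentages rest on the assumed effect size, SD, correlations and attrition. That the 2-df test does not isolate F24 rests on none of them. It does not follow that the trial will misreport maintenance: an intended but unwritten F24 comparison would prevent it. The defect is that the rule allowing a maintenance statement on these outcomes is not tied to the 24-month visit, although it is for the primary outcome.

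**What to change.** Keep the three-visit mixed model. For each secondary outcome analysed with it, name the 1-df contrast intervention × (F24 − PRE), reported with its 95% confidence interval, as the test of maintenance, in line with the primary outcome. State that only this contrast supports a maintenance statement, and enter its p value in the Hochberg set for the long-term analyses.

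The cost is a sentence or two in the analysis section, with the same data, model and software. Where an effect is fully kept, the contrast has somewhat less power than the interaction: for 0.5 SD at correlation 0.5, 72% against 74%, both before multiplicity adjustment.
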